### Usual care (control) group

Participants randomised to usual care will receive the usual advice provided by haematology CNSs. Participants who specifically ask the research team for exercise advice will be signposted to generic PA advice offered for people undergoing cancer treatment on the Macmillan Cancer support website^34^ or from the information and support service within UCLH.

During hospital admission, patients undergoing SCT are routinely screened by a hospital physiotherapist and receive input for any functional or mobility-related deficits that may prevent or delay hospital discharge. All patients within the study who require physiotherapy or occupational therapy during their hospital admission will receive input as indicated. The indication for and details of input required will be obtained from participants’ hospital records and recorded in the study file for enrolled participants who require additional therapy input. Control group participants will not be asked to monitor their activity or receive log books.

### Outcome assessment

The primary end points of this pilot study will be study feasibility. A target recruitment rate of >50% of potential participants screened as eligible and approached for this study will be a primary indication of feasibility. Feasibility of delivering the intervention protocol will be assessed by evaluating adherence to the intervention and acceptability of receiving the intervention (including deviations from exercise protocol). Attrition due to the intervention, loss to follow-up and adverse events will also be assessed.

A number of secondary end points will also evaluate any between group differences and determine intended primary and secondary end points for a fully powered trial. Fatigue will be assessed using the Functional Assessment of Chronic Illness Therapy (FACIT-F) questionnaire.^35^ QOL will be measured with two complementary instruments: the European Organisation for Research and Treatment of Cancer QOL Questionnaire (EORTC QLQ-C30 and myeloma-specific module QLQMY20)^36 37^ and the Functional Assessment of Cancer Therapy Bone Marrow Transplantation (FACT-BMT) scale questionnaire.^38^ The EORTC QLQ C-30 has a focus on physical and functioning dimensions of QOL whereas FACT-BMT can assess impact of treatment and side effects on QOL. Comparison analysis indicates that both instruments should be used together rather than in place of each other when assessing QOL in patients undergoing SCT.^39 40^

Functional capacity will be assessed with a 6 min walk test (6MWT), handheld dynamometry and a timed sit-to-stand test. PA and sedentary time will be recorded over 5–7 days using an ActivPAL accelerometer (PAL Technologies, Glasgow, UK). Additional measures of self-reported PA behaviour will be captured using the self-complete short form International Physical Activity Questionnaire^41^ and the Exercise Self-Efficacy Scale.^42^ All these measures will be recorded at baseline and three time points during the ASCT pathway. At the final time point, an adapted Client Service Receipt Inventory questionnaire will be used to assess health and social care usage in the time following hospital discharge.^43^

The outcomes measures and time points for data collection are summarised in table 2.

**Table 2 T2:** Study schedule of assessments

Visit no.	Screening	Baseline assessment (T0)	Follow-up 1 (T1)	Follow-up 2 (T2)	Follow-up 3 (T3)
		1	2	3	4
	On referral to UCLH ASCT MDT	On day of first transplant clinic appointment	Day of transplant	Day of discharge from hospital	Post-transplant follow-up clinic at 3 months
Qualitative interview (~20 patients who decline study)	X				
Window of flexibility for timing of visits		±2 days	0±1 day	0±1 day	±5 days
Screening eligibility	X				
Informed consent		X			
Demographics and clinical history		X			
Fatigue: FACT-F		X	X	X	X
QOL: EORTC QLQ C-30-MY20		X	X	X	X
QOL: FACT-BMT		X	X	X	X
Exercise behaviour: IPAQ-SF		X	X	X	X
Exercise Self-efficacy Scale		X	X	X	X
Functional capacity: 6MWT		X	X	X	X
Functional capacity: 30 s STS		X	X	X	X
Functional capacity: handheld dynamometry		X	X	X	X
Resting BP and HR		X	X	X	X
Height and weight		X	X	X	X
Accelerometery (3–7 days)		X	X	X	X
Qualitative interview (20 participants)					X
Health and social care service use: CRSI					X
Blood counts		X	X	X	X
Levels of immune function (blood)		X	X	X	X

ASCT, autologous stem cell transplant; BP, blood pressure; EORTC QLQ C-30-MY20, European Organisation for Research and Treatment of Cancer QOL Questionnaire and myeloma specific module; CRSI, Client Service Receipt Inventory; FACT-BMT, Functional Assessment of Cancer Therapy Bone Marrow Transplantation; FACT-F, Functional Assessment of Chronic Illness Therapy Fatigue questionnaire; HR, heart rate; IPAQ-SF, International Physical Activity Questionnaire short form; MDT, multidisciplinary team; 6MWT, 6 min walk test; QOL, quality of life; STS, sit to stand; UCLH, University College London Hospitals NHS Foundation Trust.

### Qualitative data

Semi-structured interviews will be conducted with a purposeful sample of participants at two time points. Study ‘decliners’, deemed eligible for the study, who have received a study PIS but declined to enrol in the study will be asked if they would participate in a short interview. These interviews will take place either face to face in the clinic setting or via telephone (based on participants’ preference) and will be conducted to explore the patients’ experiences of being approached for the exercise study and the process and outcome of their decision-making process in relation to the exercise study.

Additional semi-structured interviews from approximately 20 participants who enrol and take part in the study will take place at final follow-up, approximately 3 months post-transplant, and will be conducted to explore the participants experiences of ASCT treatment and their experiences of being enrolled in the study. Participants will be purposively sampled to include participants from both the intervention arm and the control arm.

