### Objectives

This primary aim of this pilot, single-centre, RCT is to investigate the feasibility of a physiotherapist-led exercise intervention as an integral part of the ASCT pathway for patients with myeloma. It is hypothesised that this intervention, delivered before and during ASCT treatment for myeloma, will be feasible in terms of recruitment rate and willingness of the participants to be randomised, intervention adherence, compliance to the exercise prescription and attrition due to the intervention.

Primary objectives of the pilot study are to measure eligibility and recruitment rates from potential participants screened on referral to myeloma outpatient clinics for consideration for ASCT; acceptability of the intervention, including adherence to exercise sessions and deviations from exercise protocol; study completion rate and any adverse events.

Secondary objectives are to collect preliminary data on the intended primary/secondary outcomes of a future fully powered RCT to obtain mean and SD estimates to inform a sample size calculation. These outcomes include: cancer-related fatigue; QOL; levels of PA and sedentary time; functional capacity and muscle strength; hospital length of stay, rates of readmission and health service utilisation and if the trial/exercise intervention is delivered as intended.

Exploratory objectives are to investigate any effect on immune parameters (including immunoglobulins, T cells, B cells, natural killer cells).

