## Ethics and dissemination

All participants will provide informed written consent to take part and can withdraw at any time.

Results of this study will be written up as part of a doctoral thesis and disseminated through publication in peer-reviewed journals, presentation at haematology and rehabilitation-related meetings and shared locally. A lay summary of the study results will be provided to participants who request to receive one after the study has completed.

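### Enrolled participants are interviewed only at the final follow-up, so the interviews leave out anyone who withdraws or is lost before it

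*Protocol article*

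**What the plan says.** Two interview groups are described under Qualitative data. The first is eligible patients "who have received a study PIS but declined to enrol in the study will be asked if they would participate in a short interview"; Table 2 puts this at screening, for about 20 people. The second is drawn from people who enrol: "Additional semi-structured interviews from approximately 20 participants who enrol and take part in the study will take place at final follow-up". Its sampling is described in one sentence: "Participants will be purposively sampled to include participants from both the intervention arm and the control arm". In Table 2 (Outcome assessment) the row "Qualitative interview (20 participants" has a single mark, under T3, the clinic visit three months after transplant.

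Under Ethics and dissemination, participants "can withdraw at any time". The primary objectives (Objectives) include "acceptability of the intervention, including adherence to exercise sessions and deviations from exercise protocol". Outcome assessment says that feasibility of delivery is judged by "evaluating adherence to the intervention and acceptability of receiving the intervention (including deviations from exercise protocol", and adds: "Attrition due to the intervention, loss to follow-up and adverse events will also be assessed".

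**The concern.** Acceptability is a primary objective, and the hypothesis under Objectives names attrition caused by the intervention as a feasibility criterion. The Discussion links success of the pilot to a fully powered multicentre trial. For that decision, the reasons why people try the programme, or accept randomisation, and then leave are among the most useful things the pilot could learn. The interviews are the part of the design best suited to drawing out those reasons, yet their timing selects on having stayed. The plan already values the views of people who say no, since it interviews decliners. It makes no matching provision for people who say yes and then leave.

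**Working it through.** No formula applies, and the plan has no figure of its own to reproduce. The check sets the statements side by side.

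1. **Who can be interviewed.** Decliners did not enrol. The second group enrolled and is seen at T3. Someone who enrolled and left the study before T3 satisfies neither condition. The text and Table 2 agree on the timing, so this follows from a stated rule and not from a missing detail.

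2. **How long the gap is open.** Baseline is about 6–8 weeks before transplant (Abstract), and T3 is about 12 weeks after transplant or discharge. Counted from transplant, that is 6 + 12 = 18 to 8 + 12 = 20 weeks. Counted from discharge, the admission is added.

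3. **How many people it could be.** Recruitment is put at 60–75 (Recruitment procedures). No dropout rate is given. Assuming 10% to 30%:
   - low end: 0.10 × 60 = 6
   - high end: 0.30 × 75 = 22.5, so about 22

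   This range shows scale only. Some of these people may leave for clinical reasons and be unable to give an interview.

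4. **Who is not in the gap.** A participant who stops exercising but stays in follow-up can be interviewed at T3. Intervention says that inpatient sessions may be declined, and it does not treat this as leaving the study. For these people the weakness is narrower: no stated sampling factor ensures that low adherers are chosen.

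5. **What other sources say about leavers.**
   - Log books (Intervention) ask how participants feel after exercise and why prescribed exercise was not done. They cover the period before stopping, but depend on self-completion, and their contents are reviewed with the physiotherapist who delivers the programme (Table 1).
   - The physiotherapist's record of declined or impossible sessions is described for the inpatient phase.
   - Weekly contact is planned in the phases before admission and after discharge.
   - Data analysis covers dropout, completion of assessments, and use of and satisfaction with materials. Dropout and completion rates count leavers but do not explain them.
   - Control participants receive no log book (Usual care). Data analysis nevertheless plans to judge the acceptability of randomisation through dropout. For a control participant who leaves because of allocation, the article describes neither a log book nor an interview.

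Leavers are therefore partly visible in the quantitative and log-book data, more so in the exercise arm, and absent from the interviews.

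**The case against.** The strongest reply is that the interviews are a supporting strand. Objectives and Outcome assessment describe acceptability through adherence and deviations, with attrition and loss to follow-up assessed alongside, and Outcome assessment does not name the interviews as an acceptability measure. Their stated purpose is to explore experiences of transplant and of being in the study, in both arms. That stands, and it rules out two inferences a reader might draw. One is that the acceptability finding as a whole rests on people who stayed. It does not, because adherence, deviations and attrition can count leavers. The other is that leavers are never heard. Log books, physiotherapist records and weekly contacts capture some of their reasons, though less fully than an interview and chiefly in the exercise arm.

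A second reply is that the article condenses a fuller protocol, and that saying the sample will include both arms does not exclude other sampling factors. That has force for the sampling factors. It has less for the timing, which the article states explicitly and consistently in two places.

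A third reply is that reserving places for leavers thins a small sample, and that an approach soon after leaving could reach people while they are unwell. Both are fair and are allowed for in the fix.

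**Conclusion.** The point holds for the interview component only. As scheduled, it excludes participants who withdraw or are lost before T3, so its themes on the experience of the study and on reasons for leaving are those of people who reached T3. This rests on reading the T3 timing as the whole plan for enrolled participants; a fuller protocol that already invites withdrawers would resolve it.

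The likely direction is that problems serious enough to make people leave will be under-represented. The size cannot be derived: the only scale available is the 6 to 22 people above, under an assumed dropout of 10% to 30%. No biased percentage should be attached to it either, since the interviews are a purposive sample analysed thematically and do not estimate a proportion. The randomised comparison and the quantitative feasibility measures are not undermined. This is a worthwhile, inexpensive improvement to the evidence on a primary objective.

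**What to change.** - Keep the total at about 20 interviews with enrolled participants.
- Add adherence and withdrawal status as sampling factors alongside arm.
- Invite participants in either arm who leave the study before T3 to a telephone interview near the time of leaving, when they are well enough. Obtain consent to this contact at enrolment. Telephone is already an option for decliners.
- Amend the Table 2 row so that the timing reads *T3, or at study withdrawal*.
- Report themes from completers and leavers separately. If no leavers agree, describe the themes as those of completers.

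The cost is a minor amendment to the schedule and consent wording, with no increase in the number of interviews. There will be fewer completer interviews: if five or six of 20 places went to leavers, 14 or 15 would remain, about seven per arm if split evenly. Some leavers will refuse.

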### Anticipated dates of trial commencement and completion

Recruitment commenced in June 2019, with data collection for all follow-up assessments estimated to be completed by December 2020.

### Statistical analysis including sample size calculations

This is a pilot study with no formal power calculation. There is limited available data on the application of an exercise intervention delivered prior to ASCT in people with myeloma. This study will provide estimates of means/SD for the intended outcomes of a fully powered RCT, to support a sample size calculation for a larger trial. Meaningful clinically important differences are known for a number of the secondary end points, including the FACIT-F,^44^ EORTC-QLQ-30 and MY20 module^45 46^ and 6MWT^47^ and will be used to inform future sample size calculations. For a pilot study, including >30 participants in each arm is considered to be an acceptable number.^48 49^

### Data analysis

The primary outcomes (intervention recruitment rate and intervention adherence) from the trial will be summarised as percentages or mean values for each item, with 95% CIs. Data on the acceptability of the randomisation through its effect on dropout rates, completion rates of the outcome assessments and reported use and satisfaction with the intervention materials will also be analysed descriptively. Group differences in fatigue, QOL, functional capacity, PA and sedentary time, self-efficacy at each time point will be analysed using linear regression for continuous factors (eg, fatigue) and frequency tables, χ^2^ tests and logistic regression for categorical factors. Gender and age will be included within the models as covariates. Repeated measures analyses (eg, mixed models) will be used to analyse the baseline and follow-up scores of all measures together. Assessments for each outcome will be made to determine whether the data are normally distributed. For outcomes that are not, even after appropriate transformations, non-parametric methods will be used for data analyses at specific time points.

Qualitative data derived from the interviews of patients will be analysed thematically using an approach that is both deductive and inductive to ensure that the full range of participants' responses are represented. Codes generated from the data will be assigned to portions of the text to develop an initial coding framework, which will be used by another researcher familiar with the sample population to independently double-code a proportion of the interview transcripts. The framework will be revised to ensure that the codes accurately reflect the data and any discrepancies will be resolved via discussion. The final codes will be applied to the data and incorporated into appropriate themes/subthemes.

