Resistance exercises will be prescribed to target all major muscle groups (depending on individual health and contraindications). Resistance training will be performed using body weight, progressed with weights or using elastic resistance bands of various strengths. These bands will be supplied to participants at the start of the study to allow convenient independent resistance training. Starting resistance and repetitions of the exercises will be informed by a 10-repetition maximum assessment carried out by the physiotherapist during the first session. Individually tailoring and gradual progression in resistance training will be prescribed as deemed appropriate at each exercise session by the physiotherapist according to published principles.^28^ Participants will be provided with exercise log books and asked to record what exercise they do in the books, as well as document how they feel after exercising and any reasons for not carrying out the exercise as prescribed.

In phase 2, when participants are admitted to hospital for their ASCT, they will be offered supervised exercise with the physiotherapist three times per week in the ambulatory care or hospital ward setting (depending on each participant’s clinical location), which they can decline if they wish to do so. It is anticipated that participants will be symptomatic from the effects of their ASCT, which may include nausea, gastrointestinal complaints and fatigue. They may also experience bleeding and infection as a result of thrombocytopenia and low white cell counts. Therefore the exercise intervention will be highly individualised and tailored according to participant’s capacity to carry out the exercises. Aerobic exercise will be carried out, as able, on a stationary bike in bouts of 10 min, up to a total duration of 30 min. HR will be monitored throughout and participants will be guided to exercise at a RPE (determined by RPE scale) they are comfortable with. Any exercise undertaken, declined or not possible due to clinical indication will be recorded by the physiotherapist in the participants’ log book.

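### Group differences at T1 and T2 are taken from per-visit regressions without the baseline score; the mixed model already planned should be named as their source

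*Protocol article*

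**What the plan says.** The Data analysis section sets out two analyses of the secondary outcomes.

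- **Per visit.** Differences in fatigue, quality of life, functional capacity, activity and self-efficacy "at each time point will be analysed using linear regression for continuous factors (eg, fatigue"). On adjustment it says "Gender and age will be included within the models as covariates". The baseline score is not named.
- **All visits.** "Repeated measures analyses (eg, mixed models) will be used to analyse the baseline and follow-up scores of all measures together".

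The article does not say which of the two supplies the reported differences. The sample size section gives the estimates a use: "This study will provide estimates of means/SD for the intended outcomes of a fully powered RCT, to support a sample size calculation".

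Table 2 (Outcome assessment) places the follow-ups at "Day of transplant Day of discharge from hospital Post-transplant follow-up clinic at 3 months", with windows of "0±1 day 0±1 day ±5 days". The walk test, sit-to-stand and dynamometry are due at every one of them. On the admission, the Intervention section says: "It is anticipated that participants will be symptomatic from the effects of their ASCT, which may include nausea, gastrointestinal complaints and fatigue". Data analysis also promises that "completion rates of the outcome assessments and reported use and satisfaction with the intervention materials will also be analysed descriptively".

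**The concern.** A regression on one visit's score can use only people who have a score at that visit. T1 and T2 are the visits at which a participant is most likely to be too unwell for a walk test or a sit-to-stand test, and the narrow window leaves little room to rebook. If those who miss the test tend to be less fit, the observed mean is too high and the observed SD too small. If fewer are missing in the exercise arm, that arm also keeps more of its weaker members and the difference shrinks.

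Two things are at stake: the preliminary between-group differences, and the means and SDs passed to the later trial. There is also a plain loss of precision, because everyone has a baseline score and the per-visit models as described do not use it.

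**Working it through.** The plan has no figure to reproduce: it states that there is no formal power calculation and gives no missing rate, SD or baseline correlation. The check therefore shows the mechanism under stated assumptions.

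**Assumed inputs.** Outcome standardised to SD 1; true difference 0.30 SD; missing in control v exercise 15% v 10%, 20% v 10% or 25% v 15%; correlation ρ between function and being testable 0.5 (range 0.3–0.6); correlation r of baseline with follow-up 0.5–0.7.

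**Formulas.** For missing proportion m, with z the standard normal quantile of m and φ the normal density:
- λ = φ(z)/(1 − m). This is 0.195, 0.274, 0.350 and 0.424 for m = 10, 15, 20 and 25%.
- Observed mean too high by ρλ.
- Observed SD = √(1 − ρ²λ(λ − z)).
- Observed difference = 0.30 − ρ(λ_control − λ_exercise).

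**Per-visit difference when missingness depends on the unseen score, ρ = 0.5**

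| Missing, control v exercise | Observed difference | Control SD |
|---|---|---|
| 15% v 10% | 0.30 − 0.5(0.274 − 0.195) = 0.26 | 0.95 |
| 20% v 10% | 0.30 − 0.5(0.350 − 0.195) = 0.22 | 0.95 |
| 25% v 15% | 0.30 − 0.5(0.424 − 0.274) = 0.22 to 0.23 | 0.94 |

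Over ρ = 0.3–0.6 the difference runs from 0.21 to 0.28. The control SD runs from √(1 − 0.09 × 0.274 × 1.311) = 0.98 (15% missing) to √(1 − 0.36 × 0.424 × 1.098) = 0.91 (25% missing). Squared, that is 0.97 to 0.83, so a sample size built on this SD would be about 3–17% too small.

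**Two limits.** With equal missingness in both arms the λ terms cancel and the difference stays at 0.30; with ρ = 0 there is no bias at all. If the only cause of unequal missingness is the 0.30 SD effect itself, the exercise quantile becomes z − 0.3ρ. With ρ = 0.5 and 25% missing in control, about 20.5% are then missing in exercise and the observed difference is 0.27.

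**What using the baseline changes.**
- *Missingness depends on the observed baseline.* The per-visit loss is rρ(λ_control − λ_exercise), so at ρ = 0.5 the observed difference is 0.25–0.28. Conditioning on baseline restores 0.30.
- *Missingness depends on the unseen score.* The loss is multiplied by (1 − βr), where β = r(1 − ρ²δ)/(1 − r²ρ²δ) and δ = λ(λ − z) averaged over arms. For 25% v 15%, δ = 0.412 and ρ²δ = 0.103. With r = 0.7, β = 0.66 and the estimate is 0.30 − 0.0747 × (1 − 0.46) = 0.26; with r = 0.5 it is 0.24. Over all three pairs it is 0.24–0.28, against 0.22–0.26 without baseline.
- *Heavier loss (30% v 15%, 40% v 20%; ρ = 0.6; simulated).* Under baseline-dependent missingness the per-visit difference is 0.18–0.23, restored to 0.30. Under dependence on the unseen score it is 0.12–0.17, improved only to 0.16–0.23.
- *Precision.* The standard error is multiplied by about √(1 − r²): 0.87 at r = 0.5 and 0.71 at r = 0.7.

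**The case against.** The case against is substantial. The mixed model is in the same paragraph, covers all measures and keeps participants who miss a visit; the article nowhere says that the visit differences exclude it. Missing-data rules are commonly left to a full protocol or SAP that is not shown. Completion rates are already to be reported. Fatigue, quality of life and self-efficacy are questionnaires and need no physical test. The symptom sentence explains why inpatient exercise is tailored; it does not say that assessments will be missed. Known clinically important differences will inform the later sample size, so that trial need not rest on the pilot's observed difference. The primary feasibility endpoints are untouched.

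Most of this stands, and it limits the point. A reader might infer that the T1 and T2 results will describe only the fitter participants. That would need a fixed level of function below which nobody can be tested, and nothing in the article supports one. Nor is it right that group differences come solely from the separate regressions, or that the mixed model would cure all selection.

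What survives is not a missing detail. The article does assign visit-specific differences to a regression, names its covariates without the baseline score, and gives the better analysis no stated role in those differences or in the means and SDs.

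**Conclusion.** The point holds as a choice of main analysis. The per-visit regressions are the weaker of two analyses already planned, and they are the one attached to the visit differences. Whether they mislead depends on how many tests are missed, how closely that is tied to health, and whether it differs by arm; the documents are silent on all three. Under the moderate assumptions above the attenuation is 0.04–0.08 SD of a true 0.30, and the SD is 2–9% too small. The exposure is mainly in the performance tests and less in the questionnaires. The gain in precision from the baseline score does not depend on any missing data. The matter is worth correcting, but it does not threaten the feasibility conclusions.

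**What to change.** State that the T1, T2 and T3 differences, and the means and SDs passed to the future sample size calculation, come from the planned mixed model: baseline and follow-up scores, arm-by-visit terms, gender and age, and all randomised participants with any score. Give both arms a common baseline mean, or enter baseline as a covariate; otherwise the precision gain is not obtained. Keep the per-visit regressions as a sensitivity analysis.

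Because the model only partly corrects for missingness that depends on the unseen score, report the completion rates already planned by arm, visit and reason (unable for health reasons, or other), beside the estimates.

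The cost is a few lines of analysis wording and one reason-for-missing field per test. Outcomes that stay non-normal after transformation would still go to the non-parametric visit-specific methods already foreseen, and should be labelled as based on observed scores only.

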### Recruitment procedures

A participant information sheet (PIS) detailing the study will be provided in a clinical information pack routinely posted to patients prior to their first routine transplant clinic appointment. Potential participants will be contacted by the principle researcher or study physiotherapist, with a follow-up telephone call to allow patients to ask questions about the study. Those who wish to proceed will be asked to provide informed consent and this will be recorded on the participant consent form. Those approached to take part in the study who are subsequently found to be ineligible or decline to take part will be recorded in a screening log by the principle investigator.

It is conservatively estimated that approximately 60–75 patients will be recruited over a 15–18-month period, with completion of final follow-ups within 18–21 months. Approximately 100 myeloma patients undergo ASCT at UCLH each year.

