### Randomisation procedures and blinding

Participant randomisation will be undertaken centrally by a researcher not involved in outcome assessment or intervention delivery, using minimisation, with age and gender as the stratification factors using MinimPy, a free, open-source, desktop programme (https://sourceforge.net/projects/minimpy/). This researcher will communicate their allocation of participants to the physiotherapist who will inform participants of the allocation and deliver the intervention to those in the intervention arm. The principle investigator will attempt to remain blinded to group allocation and will conduct follow-up outcome assessments.

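### The regressions at each time point adjust for age and gender but not for the outcome's own baseline value, which gives up precision in the secondary group comparisons

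*Protocol article*

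**What the plan says.** The Data analysis section of the protocol article plans two analyses of the secondary outcomes.

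- **Time-point comparisons.** "Group differences in fatigue, QOL, functional capacity, PA and sedentary time, self-efficacy at each time point will be analysed using linear regression", with logistic regression among the methods for categorical outcomes. The covariates are then named: "Gender and age will be included within the models as covariates".
- **Repeated measures.** "Repeated measures analyses (eg, mixed models) will be used to analyse the baseline and follow-up scores of all measures together". The article does not say how the group effect is defined in this model, or which of the two analyses takes precedence.

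On measurement, Outcome assessment says of the scales and tests concerned: "All these measures will be recorded at baseline and three time points during the ASCT pathway". Table 2 agrees, with entries at T0, T1 (transplant), T2 (discharge) and T3 (three-month clinic). Service use differs: "At the final time point, an adapted Client Service Receipt Inventory questionnaire will be used to assess health and social care usage".

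On allocation, Randomisation procedures and blinding describes "using minimisation, with age and gender as the stratification factors". On size, Recruitment procedures expects that "approximately 60–75 patients will be recruited over a 15–18-month period", and the sample size section adds: "For a pilot study, including >30 participants in each arm is considered to be an acceptable number".

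**The concern.** For a scale or walk test measured repeatedly in the same patient, the baseline value is usually the best available predictor of the follow-up value. Here it is scheduled for every outcome in the regression sentence, yet the stated covariate list leaves it out. Nothing in the allocation balances it either, except through whatever relation it has with age and gender.

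Two things follow for the time-point regressions. The confidence intervals are wider than they need to be. And if the arms happen to differ at T0, part of that difference carries through to the estimate at T1, T2 and T3. Outcome assessment says the secondary end points are to examine group differences and help choose the end points of the main trial, so the quality of these estimates has some bearing on what comes next.

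**Working it through.** The plan has no power calculation or stated precision to reproduce, so the check is of precision in SD units.

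**Inputs**

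- Patients per arm: 30 to 37, from a total of 60 to 75. A 1:1 ratio is assumed, as none is stated. The guidance of more than 30 per arm is met only from 62 in total.
- r, the correlation between T0 and follow-up: not given in the documents. The range 0.3 to 0.7 is an assumption.
- Equal SDs at T0 and follow-up and complete data are assumed. Any explanatory effect of age and gender on the residual SD is ignored. The figures apply to the continuous outcomes.

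**Step 1: precision with and without T0**

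Without T0, SE = √(2/n). At n = 30 this is √(2/30) = 0.258 SD. The model has an intercept, group, age and gender, so 60 − 4 = 56 df and t = 2.003. The half-width is 2.003 × 0.258 = 0.517 SD.

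With T0 as a covariate, the SE is multiplied by √(1 − r²). The loss of one further df is negligible. The equivalent number per arm without T0 is 30/(1 − r²).

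| r | √(1 − r²) | Half-width, n = 30 | Variance saved | Equivalent n per arm |
|---|---|---|---|---|
| no T0 | 1 | 0.52 | – | 30 |
| 0.3 | 0.954 | 0.49 | 9% | 33 |
| 0.5 | 0.866 | 0.45 | 25% | 40 |
| 0.6 | 0.800 | 0.41 | 36% | 47 |
| 0.7 | 0.714 | 0.37 | 49% | 59 |

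At n = 37 the half-width is 0.46 SD without T0, and 0.44, 0.40, 0.37 or 0.33 SD with it.

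**Step 2: chance imbalance at T0**

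The difference between arms at T0 has SD √(2/30) = 0.258 SD under randomisation. The chance that it exceeds 0.25 SD in either direction is 2 × [1 − Φ(0.25/0.258)] = 33% per outcome (28% at n = 37). For 0.5 SD it is 5% (3% at n = 37).

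Given a T0 difference d, an estimate without T0 shifts by r × d. For d = 0.25 SD that is 0.075, 0.125, 0.15 or 0.175 SD at r = 0.3, 0.5, 0.6 or 0.7.

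**Step 3: does the repeated-measures analysis make up for it?**

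That depends on the contrast, which is not stated.

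- *Raw group difference at a visit, baseline means free in each arm:* shift r × d, as in the regression.
- *Change from T0 (group by time), baseline means free:* shift (r − 1) × d. At r = 0.6 and d = 0.25 this is −0.10 SD, against +0.15 SD for the regression. The variance is multiplied by 2(1 − r): 1.4, 1.0, 0.8 or 0.6 at r = 0.3, 0.5, 0.6 or 0.7. The covariate gives 0.91, 0.75, 0.64 or 0.51.
- *T0 as covariate, or a common baseline mean across arms:* about the full gain in Step 1.

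A simulation of 20,000 trials with 30 per arm and r = 0.5 gave SEs of 0.259 without T0, 0.226 with T0 as covariate, and 0.257 for change from T0. The first and third are nearly the same, as the factor 2(1 − 0.5) = 1.0 predicts.

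**The case against.** The strongest reply is that baseline is not ignored, because the repeated-measures sentence brings it in for all measures. That stands, and a reader who took the plan as wholly unadjusted would be wrong. It does not repair the time-point regressions, whose covariates are stated outright rather than left to another document. As Step 3 shows, whether the mixed model helps depends on its contrast. The article's silence on that detail is not itself a fault, since a full analysis plan may settle it.

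Four other stronger readings are tempting and are not supported.

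- *The mixed model has the same imbalance problem.* This is true only of a raw difference at a visit. A change-from-T0 contrast shifts in the opposite direction, and by a different amount unless r = 0.5.
- *The group estimates are biased.* Allocation is randomised, so there is no systematic bias. The shift in Step 2 is conditional on a chance imbalance.
- *An inflated residual SD will be handed to the main trial.* Objectives and the sample size section promise means and SDs of the outcomes. These are descriptive and do not depend on the regression covariates. No section says that a residual SD is carried forward.
- *Every outcome has a T0 value.* The outcomes in the regression sentence do. Service use, length of stay and readmission do not.

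It is also fair to say that r may be low at some visits. T2 is the day of discharge after transplant, when the Intervention section expects patients to be symptomatic. At r = 0.3 the gain is small, from 0.52 to 0.49 SD. Finally, the primary end points are feasibility measures and no stated decision rule rests on these comparisons. That limits the importance of the point but not its correctness.

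**Conclusion.** The point holds for the time-point regressions. Their named covariates omit the T0 value of outcomes that are all measured at T0, and minimisation does not balance those values. At 30 per arm this leaves a half-width of about 0.52 SD where 0.49 to 0.37 SD would be available, and a one-in-three chance per outcome of a T0 difference above 0.25 SD that the model does not address. The size rests on an assumed r of 0.3 to 0.7, 1:1 allocation and complete data. Attrition would widen all the intervals. The consequence is modest: less precise secondary estimates in an unpowered feasibility pilot. It is still worth correcting because the remedy needs no new data.

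**What to change.** In Data analysis, do one of the following for outcomes that have a T0 value:

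1. Add the outcome's T0 value as a covariate, beside age and gender, to the regressions at T1, T2 and T3. It cannot apply to a comparison at T0 itself.
2. Take the T1 to T3 group differences from one mixed model per outcome, with T0 as a covariate or with a common baseline mean across arms. This also gives one answer per outcome.

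Alongside the descriptive means and SDs, report the T0-to-follow-up correlation for each outcome and visit. A main trial that adjusts for baseline can then multiply its unadjusted sample size by 1 − r².

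The cost is a change of wording, since T0 assessments are already scheduled. One practical matter is that a patient without a T0 value drops out of a covariate model unless that value is handled. The common-baseline model keeps such a patient.
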